### Data monitoring committee

As the procedure cannot cause any adverse effects, no early termination is planned.

Data quality control on the case report form during statistical analysis will be performed to ensure that the data are complete, consistent, and plausible. In the event of an anomaly, the investigator will be asked to correct it. If a check is required in a source document, it can only be done by a member of the supervisory medical team.

An audit may be carried out at any time by persons designated by the sponsor and independent of those responsible for the research. The persons leading and monitoring the research agree to comply with the sponsor’s audit requirements. Verification can be applied at all stages of the research, from the development of the protocol to the publication of results and the classification of data used or produced in the research.

Any event resulting from a breach of protocol, standard operating procedures or applicable laws and regulations by an investigator, or any other person involved in the conduct of the research shall be subject to a no-action promoter compliance report (Assistance Publique – Hôpitaux de Paris). These non-conformities will be managed in accordance with the sponsor’s procedures.

The final report of the research with the human person referred to in Article R1123-67 of the CPMP shall be prepared and signed by the sponsor and the investigator. A summary of the report shall be prepared in accordance with the reference plan of the competent authority and shall be sent to the latter within one year of the end of the research, corresponding to the end of the participation of the last person having lent himself to the research.

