### Participants

The patients will be recruited during their visit to the day hospitalization section of the Diagnosis and Therapeutic Center of Hôtel-Dieu University Hospital, for hypertension-related complications and cardiovascular risk assessment as part of their hypertension management.

Participants will be eligible if they are at least 18 years of age, diagnosed with hypertension (treated or untreated), followed by a MD in the structure for hypertension management, and able to provide written informed consent. Hypertension is defined by BP ≥ 140/90 mmHg by office BP measurement and/or BP ≥ 135/85 mmHg by home BP monitoring.

The non-inclusion criteria will be patients under 18 years old, APN follow-up prior to day hospitalization, pregnancy, guardianship/curatorship, or inability to give free informed consent.

Written information and oral explanations will be given to patients. To complete their inclusion in the study, free informed and written consent will be collected from each participant during the day of hospitalization.

The dropout criteria will be an acute cardiovascular event during the study period and/or therapeutic adjustment of hypertension treatment by another health professional than the APN or MD referent during the study period and/or refusal to proceed in the study.

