### Outcomes

All outcomes will be evaluated on a timeframe of 2–12 months depending on the period between the day of hospitalization (inclusion visit) and the MD consultation (final visit of the study).

The primary outcome will be:Rate of controlled BP in MD consultation by office BP measurement

According to the European and International guidelines, the protocol for office BP measurement will be 5 min rest, 3 measurements at 1-min intervals in a supine position followed by 3 standing measurements at 1-min intervals for orthostatic hypotension test [1–4]. Unattended office BP measurement will be conducted by a supervisor (usually a nurse), who will explain the protocol to the patient before letting him rest in a quiet room: an automatic sphygmomanometer that will print the measurement statement at the end of the monitoring session. BP level will be estimated by the average of the last two BP measures in the supine position. BP will be considered as controlled with systolic BP < 140 mmHg and diastolic BP < 90 mmHg [1–4].

As a reminder, only the BP level by office BP measurement during the MD consultation (final visit of the study) will constitute the primary outcome.

The secondary outcomes will be:Rate and quality of home BP monitoring brought to MD consultation.

According to the 2020 International Society of Hypertension (ISH) Global Hypertension Practice Guidelines, the protocol for home BP monitoring will be 3-day monitoring with a cycle of 3 measurements every morning and every evening at 1-min intervals, in a sitting position, after 5 min of rest and before meals [1]. Quality will be assessed by the number of measurements (18 measurements over 3 days).2)Therapeutic adjustments (and their indication(s)) will be collected in the medical file due to the traceability of the prescriptions of antihypertensive treatment and the APN intervention report.3)Difference in rates of controlled BP between day hospitalization and MD consultation in each group. Note that BP level during day hospitalization is measured with the same protocol as during MD consultation.

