**Fig. 2 Fig2:**
[figure not shown]
Plan for the APN intervention

The APN intervention will be performed by the same APN hypertension specialist and will last approximately 45 min to 1 h.

First, the APN will proceed to office BP measurement. The APN will explain the procedure for office BP measurement, check the correct functioning of the automatic sphygmomanometer, and install the patient in a quiet room to minimize unattended results. As described above, office BP will be measured according to the latest recommendations: 5 min of rest without speaking or smoking, 3 measurements at 1-min interval in a supine position followed by 3 measurements in a standing position for orthostatic hypotension test. These measurements will be performed with an oscillometric automatic sphygmomanometer. The retained office BP measurement will be the average of the last two measurements in the supine position [1, 2, 23]. This office BP measurement will be compared to the home BP monitoring measurement. While home BP monitoring is usually considered superior, according to its quality and taking into account potential masked or white coat hypertension, either office BP measurement or home BP monitoring will be preferred by the APN to evaluate the BP level and the efficacy of the antihypertensive drugs taken during the study [1, 2].

Through a clinical exam, the APN will then assess the general statement of health, efficacy, and potential side effects of antihypertensive treatment such as lower limb edema or cough, as well as clinical manifestations of hypertension or its complications such as headache, vertigo, syncope, impaired vision, rest or exertion chest pain, dyspnea, palpitations, intermittent claudication, edema, and cold extremities. The search for side effects will be completed, if necessary, by a cardio-pulmonary auscultation and/or an electrocardiogram (ECG). The APN will immediately refer clinically unstable patients to an MD.

The most recent blood tests will be checked to assess potential side effects of antihypertensive treatment such as dyskalemia or acute kidney injury and/or cardiovascular comorbidities such as diabetes or dyslipidemia according to the latest recommendations [25].

The APN will sum up the medical history, assess the patient’s knowledge and remind him or her of the definition, the pathophysiology, the chronic aspect of hypertension, and its possible complications.

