The APN will then assess the lifestyle and advise the patient according to the latest recommendations [1–3, 23]:Salt consumption limitation (about 6 to 8 g a day)Weight reduction in the event of overweight or obesity to maintain a normal body mass index (between 18.5 and 24.9)Practice of regular physical activity of approximately 30 min a day (to be adapted according to the clinical condition of the patient)Alcohol consumption limitation to less than 14 units per week for men, 8 units per week for womenEstablishment of a diet rich in fiber and low in saturated fatSmoking cessation

Patients’ knowledge about drugs, their indications, and mechanisms will be evaluated and updated if necessary. To estimate the overall risk of drug interaction, the APN will ask the patient about a possible additional prescription or self-medication.

While posology adaptation in the event of side effects or uncontrolled hypertension will be carried out when necessary, the APN will refer the patient to the MD if an introduction of a new drug is needed.

The APN will propose to the patient a decision-making balance between benefits and risks, the objective being to encourage the patient to improve therapeutic adherence, to promote a healthy lifestyle, and to establish in coordination with the patient a treatment plan to improve adherence.

The end of the patient interview will be dedicated to unmentioned questions or subjects, requiring in-depth consideration.

The APN will give the patient a new home BP monitoring sheet with a reminder of the procedure to follow. The patient will be required to bring the results to his or her next MD consultation.

The APN intervention report will be digitally available in the patient’s electronic medical file.

If a participant does not show up for the APN intervention, we will call him/her to schedule another appointment in the limit of the data collection timeframe. If he/she still does not show up, the allocation group will remain the same. The rate of participants not having shown up for the APN intervention will be mentioned in the result.

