### Statistical analysis

Data scientists will remain blinded by means of two databases:One database for all the participants with the data of the day hospitalization and the MD consultation (including the primary outcome). To maintain blinding, the groups will be called “group A” and “group B”One database with only the data of the APN intervention, so as to perform statistical analysis specific to this stage

The primary outcome measure (difference in rate of controlled BP between “intervention” and “usual care” groups) will be analyzed using a chi-square test. A *p* value < 0.05 will be considered significant. Participants with missing data for this primary outcome will be excluded.

For secondary outcome measures, the rate of performance and quality of the home BP monitoring between the “intervention” and “usual care” groups will be analyzed using a chi-square test. The difference between average BP at baseline and at follow-up will be determined for all the patients and separately for patients in the two study groups. Differences between baseline and follow-up will be tested for significance within paired *t*-tests within each group. Proportions of therapeutic adjustments and their indications between the “intervention” group and the “usual care” group will be tested for significance using a *t*-test for independent samples. For these secondary outcomes, missing data will be replaced by the mean and the standard deviation calculated on the sample, in case of quantitative variables, and neglected for the qualitative variables.

Non-adherent participants (APN intervention missed for the “intervention” group) will be considered in the statistical analysis: the rate of non-adherent participants will be mentioned in the results.

No adjustment for baseline differences is scheduled following the randomization. Nevertheless, statistical analysis may highlight participant characteristics, which we can correlate to controlled BP. If needed, an adjustment for baseline differences will be performed at a later time.

Correlations between the performance and quality of home BP monitoring in MD consultation and controlled BP will also be analyzed.

No interim analyses are scheduled.

Statistical analysis will be carried out using the R software.

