### Strengths of the study

Considering that the study will be conducted in a European center of excellence for hypertension, participants will benefit from the latest recommandations in hypertension management.

The centralized one-to-one randomization will ensure two equivalent groups are compared and shall limit selection bias.

The study will provide a good comparison between the current hypertension management in France and future management which will include APNs.

We will specify whether the reported drug adjustments were caused by side effects and/or non-control of hypertension, the objective being to emphasize the major role of APN interventions on medication. Assessment of the proportion of drug adjustments during the APN intervention and MD consultation will highlight the relevance of maximizing the frequency of (para)medical appointments in the global monitoring of hypertension.

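### The statement that the procedure cannot cause adverse effects conflicts with the nurse's role in adjusting drugs, and the only comparison of tolerance between arms is a weak one

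*Protocol article*

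**What the plan says.** The section 'Data monitoring committee' states: "As the procedure cannot cause any adverse effects, no early termination is planned". The first half is unqualified and serves as the reason for the second.

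The section 'APN intervention' describes a visit that only the intervention arm receives. There, "posology adaptation in the event of side effects or uncontrolled hypertension will be carried out when necessary". The APN examines the patient for oedema and cough, takes standing readings, and checks recent blood tests for "potential side effects of antihypertensive treatment such as dyskalemia or acute kidney injury". The same section sets the one-month minimum delay by the time needed to judge efficacy and tolerance after a change of treatment.

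Four other places bear on harm:

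- 'Outcomes' includes "3 standing measurements at 1-min intervals for orthostatic hypotension test" in the measurement protocol for the final visit, but no listed outcome uses them.
- 'Participants' says: "The dropout criteria will be an acute cardiovascular event during the study period". Adjustment of treatment by an outside professional and refusal to continue are the other criteria.
- 'Statistical analysis' plans a test between arms, described as "Proportions of therapeutic adjustments and their indications between the" two groups. It excludes participants whose primary outcome is missing.
- 'Strengths of the study' adds: "We will specify whether the reported drug adjustments were caused by side effects and/or non-control of hypertension".

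**The concern.** The intervention works partly through drug adjustment. Better control from more intensive treatment can bring more hypotension, electrolyte disturbance or intolerance, and the protocol names such effects itself. A statement that harm is impossible cannot stand beside that description, and it should not serve as the reason for a decision on trial conduct.

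What is at stake is how a positive result may be read. If the intervention arm shows a higher rate of controlled blood pressure, the report should let the reader see whether tolerance differed. The plan offers one indirect measure of this, while a more direct one (the standing readings) is taken and not analysed.

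**Working it through.** **Step 1. The statement against the intervention.** No figure in the plan needs reproducing here, because the contradiction is textual.

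| Point | 'Data monitoring committee' | 'APN intervention' |
|---|---|---|
| Can the procedure cause harm? | No, without qualification | Side effects of the treatment are searched for by examination, standing readings and blood tests |
| Does the procedure change treatment? | Not mentioned | Yes, for side effects or for lack of control |
| Does a change of treatment affect tolerance? | Not mentioned | Yes; the minimum delay is set to allow for it |

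Both columns cannot be right.

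**Step 2. What the plan compares between arms.**

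- *Adjustments and their indications.* 'Aims' counts tolerance among the indications, and 'Statistical analysis' compares them between arms. This is a harm-related comparison with three limits. It misses any harm that did not lead to a drug change. Its sources under 'Outcomes' are the medical file and the APN report, and the latter exists in one arm only. The objective under 'Aims' is worded for the APN visit, which has no counterpart in usual care. More tolerance-driven changes in the intervention arm could therefore mean more harm or simply more looking.
- *Standing readings.* They are taken at the final visit in both arms by the same method, so ascertainment is equal among attenders. No analysis is stated.
- *Acute cardiovascular events.* They are a dropout criterion and not an outcome. If such a patient has no final reading, the missing-data rule removes that patient from the primary comparison.

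**Step 3. What a descriptive table could show.** Inputs from 'Sample size' are 165 patients per arm and a 10% loss, so 165 × 0.90 = 148.5, about 148 evaluable per arm. The rates of orthostatic hypotension are assumptions, since the documents give none.

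SE = √[p₁(1 − p₁)/n + p₂(1 − p₂)/n], and the 95% half-width is 1.96 × SE.

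For 5% versus 10%: SE = √[(0.0475 + 0.0900)/148] = 0.0305, and the half-width is 1.96 × 0.0305 = 0.060.

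| Assumed rates | Difference (points) | Half-width (points) | 95% interval (points) |
|---|---|---|---|
| 2% vs 5% | 3 | 1.96 × √[(0.0196 + 0.0475)/148] = 4.2 | −1.2 to 7.2 |
| 5% vs 10% | 5 | 6.0 | −1.0 to 11.0 |
| 10% vs 20% | 10 | 1.96 × √[(0.0900 + 0.1600)/148] = 8.1 | 1.9 to 18.1 |

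At 150 per arm, the power of a two-sided 5% test is about 29%, 38% and 68% for these three pairs.

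**Step 4. Rare events.** If no acute cardiovascular event occurred among 165 randomised patients in an arm, the one-sided 95% upper bound would be 1 − 0.05^(1/165) = 0.018. Even a count of zero would leave a true rate of up to about 1.8% possible, so the trial could not itself establish that harm cannot occur.

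**The case against.** There are five fair points on the other side.

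**The article condenses a fuller protocol.** Adverse-event collection and safety tables are commonly left to the full protocol or the analysis plan. This stands: the lack of detailed safety reporting is not in itself a finding. It does not answer the contradiction, because the article makes a positive statement that its own text refutes.

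**Harm is compared.** A reader might infer that the plan compares no harm at all between arms. The documents do not support that, because adjustments and their indications are tested between arms and the indications include side effects. The objection stands to that extent, within the limits in Step 2.

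**Patients are looked after.** A reader might also infer that safety is not overseen. The article has the APN refer unstable patients to a physician at once, has the physician assess tolerance, assigns the decision to terminate and allows audits. The disputed sentence justifies only the absence of planned early termination. Nor does the article say that outcomes were chosen because of it.

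**Cardiovascular events are not said to be removed.** The article calls these patients dropouts but does not say that their available data are discarded. Only a missing primary outcome leads to exclusion, so loss from the comparison is a risk and not a stated rule. The article also describes no systematic recording of these events, so a count may be incomplete.

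**The extra table would settle little.** With a few percent of events per arm the interval includes zero. This is correct, and is why the table is proposed as description only.

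**Conclusion.** The concern holds in a limited form. The unqualified statement is contradicted by the protocol's own account of the intervention, and the passages must be reconciled. Comparison of harm between arms is not absent, but it rests on one proxy with unequal ascertainment, while readings that would be ascertained alike in both arms have no stated use.

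The size of any difference in harm cannot be derived from the documents. Under the assumed rates, a difference in orthostatic hypotension would be estimated to within about 4 to 8 points either side (6 points for 5% versus 10%, where the interval includes zero). This assumes 148 evaluable patients per arm and that the standing readings are complete.

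The primary test and its error rate are unaffected. What changes is how far a gain in blood pressure control can be presented as a net benefit.

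**What to change.** 1. Remove the statement that the procedure cannot cause any adverse effects, and reconcile 'Data monitoring committee' with 'APN intervention'. If no early termination is still planned, give a reason that the rest of the text supports. No clinical or stopping rule is proposed here.
2. Add one descriptive table by arm, with estimates and 95% confidence intervals and no significance claim. It should give (a) orthostatic hypotension at the final physician visit from the standing readings, using a definition that the sponsor fixes before the data are seen; and (b) the number of acute cardiovascular events that triggered dropout, counted among all randomised patients as far as known, with the number whose status is unknown.
3. Present the tolerance-driven adjustments already planned beside that table, noting that the intervention arm has an extra visit at which they can be made and recorded. Where possible, show adjustments at the APN visit separately from those at the physician visit, which both arms have.

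The cost is one corrected sentence, one table and one note. The standing readings are already part of the visit, provided that they are transcribed to the case report form. The event count uses information needed to apply the dropout criterion; a complete count in patients who never return could require additional follow-up, which is why the wording is limited to what is known.

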### Statistical analysis

Data scientists will remain blinded by means of two databases:One database for all the participants with the data of the day hospitalization and the MD consultation (including the primary outcome). To maintain blinding, the groups will be called “group A” and “group B”One database with only the data of the APN intervention, so as to perform statistical analysis specific to this stage

The primary outcome measure (difference in rate of controlled BP between “intervention” and “usual care” groups) will be analyzed using a chi-square test. A *p* value < 0.05 will be considered significant. Participants with missing data for this primary outcome will be excluded.

For secondary outcome measures, the rate of performance and quality of the home BP monitoring between the “intervention” and “usual care” groups will be analyzed using a chi-square test. The difference between average BP at baseline and at follow-up will be determined for all the patients and separately for patients in the two study groups. Differences between baseline and follow-up will be tested for significance within paired *t*-tests within each group. Proportions of therapeutic adjustments and their indications between the “intervention” group and the “usual care” group will be tested for significance using a *t*-test for independent samples. For these secondary outcomes, missing data will be replaced by the mean and the standard deviation calculated on the sample, in case of quantitative variables, and neglected for the qualitative variables.

Non-adherent participants (APN intervention missed for the “intervention” group) will be considered in the statistical analysis: the rate of non-adherent participants will be mentioned in the results.

No adjustment for baseline differences is scheduled following the randomization. Nevertheless, statistical analysis may highlight participant characteristics, which we can correlate to controlled BP. If needed, an adjustment for baseline differences will be performed at a later time.

Correlations between the performance and quality of home BP monitoring in MD consultation and controlled BP will also be analyzed.

No interim analyses are scheduled.

Statistical analysis will be carried out using the R software.

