### Sample size

For primary outcome measurement, according to the preliminary results of our pilot study, we estimated the number of patients to be included in our trial. We made the hypothesis of 50% and 65% of controlled BP in the “usual care” and “intervention” groups, respectively, equivalent to a 30% increase in the rate of controlled hypertensive participants in the “intervention” group (corresponding to a 15% absolute increase or a 30% relative increase in the controlled BP rates). Assuming an equal number of patients in the two groups, a chi-squared test with a 2-sided significance level of 5%, and a power of 85%, it will be necessary to recruit 300 patients (150 per arm). With a 10% margin of loss to follow-up, 330 patients will need to be recruited (165 per arm).

Sample size calculation was performed with the SAS software (version 9.4; Institute Carry, NC).

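### The third secondary outcome is a change in the rate of controlled BP, but the analysis written for it tests the change in average BP

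*Protocol article*

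**What the plan says.** **Aims.** The third secondary objective is descriptive: how BP control evolves from the day hospitalization to the MD consultation, in each group.

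**Outcomes.** The matching third secondary outcome is "Difference in rates of controlled BP between day hospitalization and MD consultation in each group". Control is dichotomous: "BP will be considered as controlled with systolic BP < 140 mmHg and diastolic BP < 90 mmHg". The section adds that BP is measured by the same protocol at both visits.

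**Statistical analysis.** Among the secondary analyses the text says "The difference between average BP at baseline and at follow-up will be determined for all the patients", and also separately by group. It continues: "Differences between baseline and follow-up will be tested for significance within paired" t-tests, in each group. No method is named for a change in the proportion controlled. The arms are compared on control once, at the MD consultation: "The primary outcome measure (difference in rate of controlled BP between “intervention” and “usual care” groups) will be analyzed using a chi-square test".

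**The concern.** Outcome and analysis concern different variables. The outcome is a proportion, based on whether each patient is below both limits at each visit. The analysis concerns a mean in mmHg. Average BP change appears in neither the Aims nor the Outcomes section. Followed as written, the plan would produce p-values for an unlisted variable and leave the listed outcome without a stated analysis.

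Two things are at stake. First, with one quantity defined and another analysed, the choice of which to report as the third secondary result stays open until the data are seen. Second, a paired t-test inside one arm cannot isolate an effect of the APN visit. The change in either arm also contains regression to the mean, any treatment change made at the day hospitalization, the supplied tensiometer and usual follow-up. In the intervention arm it contains any APN effect as well, mixed with the rest.

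**Working it through.** The plan gives no figure for this outcome; its only design calculation concerns the primary outcome and does not bear on this point. The main check is therefore a comparison of the text.

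**1. The definitions side by side**

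| | Outcomes | Statistical analysis |
|---|---|---|
| Variable | Controlled, yes/no | Average BP, mmHg |
| Summary | Difference between two rates | Difference between two means |
| Structure | Same patients, two visits, per group | Same patients, two visits, overall and per group |
| Method | none named for this quantity | Paired t-test per group |

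The visits and groups agree; the variable does not. A paired t-test tests whether the mean change is zero. The change in a control rate depends only on the patients who switch status. If *b* patients gain control and *c* lose it among *n*, the change is (*b* − *c*)/*n*, and McNemar's statistic is (*b* − *c*)²/(*b* + *c*).

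**2. Can the two diverge?** The documents give no SD or correlation, so these are assumptions: one arm, n = 150 (the protocol's evaluable number per arm), systolic BP only, normal, SD 16 mmHg, correlation 0.5, control meaning below 140 mmHg. Rejection rates come from 4,000 simulated arms.

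- *Mean falls from 140 to 137, spread unchanged.* Control goes from Φ(0) = 50% to Φ(3/16) = Φ(0.1875) = 57%. The t-test rejects in 64% of simulations (exact noncentral t: 63%), McNemar in 37%.
- *Mean stays at 150, follow-up SD 30% smaller (16 × 0.7 = 11.2).* Control goes from Φ(−10/16) = Φ(−0.625) = 27% to Φ(−10/11.2) = Φ(−0.893) = 19%. The t-test rejects in 5%, its nominal error rate; McNemar rejects in 51%.

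The second case is constructed to show the point: the control rate changes and the t-test cannot see it. A test on the mean is not a test of the listed outcome.

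**3. What within-arm p-values would show (illustration only).** Assume two arms with identical true change and no APN effect, n = 150 each, SD of change 18 mmHg. The noncentrality is δ/(18/√150), with the critical t on 149 df.

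- δ = 5 mmHg: noncentrality 3.40, power 0.922 in each arm. Chance that exactly one arm is significant: 2 × 0.922 × 0.078 = 0.14.
- δ = 3 mmHg: noncentrality 2.04, power 0.527. Chance that exactly one is significant: 2 × 0.527 × 0.473 = 0.50.

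Varying the SD from 14 to 20 mmHg gives 38% to 50% at a 3 mmHg fall and 2% to 24% at 5 mmHg. The value 0.50 is the maximum of 2p(1 − p), reached when power is near one half, so it is an upper bound and not a typical figure.

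**The case against.** The strongest reply is that a descriptive, within-group objective needs little. Two proportions per arm suffice; control is defined, both visits use the same measurement protocol, and both sit in one database. An interval or a McNemar test could be left to an analysis plan that is not shown. This is correct for missing detail. It does not cover the mismatch, because the article does state an analysis of the baseline-to-follow-up change and states it for another variable.

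A reader might also infer that the plan is at fault for not comparing the arms, or that it means to read a significant change in one arm and not in the other as an APN effect. The documents do not support either reading. Objective and outcome are both set within each group, the primary chi-square test already compares control between arms at the MD consultation, and no section says that the within-arm p-values will be set against each other. The 50% figure measures only that possible misreading. It does not measure the mismatch.

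Last, an ANCOVA on BP would add an outcome the protocol does not list, and the Statistical analysis section schedules no baseline adjustment. This objection stands: ANCOVA is advisable only if average BP is kept, and the Outcomes section does not require it.

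**Conclusion.** The mismatch is real and follows from the text alone, without any assumption: the third secondary outcome is a paired change in a rate, and the analysis given is for a change in a mean that is not a listed outcome. It should be corrected, but its reach is limited to one descriptive secondary outcome. The primary analysis is unaffected.

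That within-arm p-values cannot isolate an APN effect is also true, but it matters only if they are read that way. The missing between-arm test is no contradiction of the objective. The figures on divergence and on one-arm significance rest on assumed SDs, correlation and falls, and serve as illustration only.

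**What to change.** In the Statistical analysis section, replace the paired t-tests on average BP, as the analysis of the third secondary outcome, with the paired change in control rate in each arm and its 95% CI, adding McNemar's test if a test is wanted.

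If average BP is to be kept, list it as a secondary outcome. Replace the within-arm p-values with the between-arm difference in BP at the MD consultation, adjusted for day-hospitalization BP (ANCOVA), with a 95% CI. State this as a planned exception to the sentence that schedules no baseline adjustment.

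The cost is wording only. Both visits' BP values are already collected, and the sample size and primary analysis do not change. The change should be made before the outcome data are analysed.
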